11.2 Statistical analysis method

Analysis and reporting of the results will follow the CONSORT guidelines for reporting randomised controlled trials. All participants who had at least 1 efficacy evaluation after randomization will be included in the analysis. Safety analyses included all patients who received at least 1 dose of study medication. The trial data will be processed and analyzed by an independent statistician, who will be blinded to participant allocation.

A non-inferiority statistical approach was used. Continuous data were compared using either the Student t test or the Mann-Whitney nonparametric test. For binary data, the 2 treatment groups were compared using the chi-square test or the Fisher exact test. The Mantel-Haenszel test was used to evaluate ordinal quantitative data.

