3.2 Sample size

In the present data of studies on the efficacy of itroconazole treating oral candidiasis, an 85% efficacy rate was assumed. To achieve 80% power with a significance level of 10%(α level, 5%; βlevel, 20%; both 1-sided), 158 participants per group would be required. To compensate for a potential 20% dropout rate, a sample size of 380 participants in total will be applied for this study.

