4.4 Recruitment

Patients will be recruited from nine dental hospitals from northern, southern, western and eastern China. The study will be staffed with a clinical research team, who will inform potential participants about the aims, methods and potential risks and benefits of this study. All the investigators from the nine centers will be trained prior to the initiation of the study. Participants will be informed that their participation is voluntary and that choosing not to participate or withdraw will not affect their care. Patients unable to understand or follow the study procedures will not be enrolled. Potential participants will be recruited to the study following signing the written informed consent including information about the trial.

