5.2 Secondary outcome measurements

• Clinical improvement rate: (score of symptom and clinical sign at baseline- score of symptom and clinical sign post treatment)/ score of symptom and clinical sign at baseline

• Mycological: Eradication of organism (negative culture and negative microscopy)*

• Safety: Number of patient withdrawals due to adverse reactions; Incidence of adverse reactions (reported as side-effects).

*Candida albicans is found routinely in asymptomatic population, therefore, it would have been inappropriate to use mycological eradication as the primary outcome measure for the study.

The cure is defined as complete clinical response and eradication of Candida spp. at Day 7 or Day 14. A complete clinical response was defined as the complete disappearance of oral candidiasis lesions, and a partial clinical response was defined as ≥60% of clinical improvement rate compared with the score at baseline. <60% of clinical improvement rate and candida persistence, re-infection or species shifts were considered failures. Finally, biologic, local, and general safety was compared between treatments.

Participants will also be required to complete their daily diaries from the start of the treatment period until the end of the treatment period. Blood tests for full blood count and liver and kidney function tests will be conducted at initial assessment and during the final clinic visit (week 4).

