8.3 Research process

Potential participants will undergo preliminary screening for eligibility during visit 1 by investigators, which will include a registered oral medicine specialist. Eligible participants will then undergo initial assessments for review of system (ROS), baseline data collection, which include the symptom scoring, grade of clinical sign of oral candidiasis, measurement of vital signs (temperature, blood pressure and heart rate. ECG), full blood count, kidney function test and liver function test. The candida-related laboratory testing (smear test and fungi culture) will be performed to gather the baseline data of candida infection and colony forming unit count. A daily diary will then be given to record the change of symptoms and occurrence of adverse events and use of topical treatments during the 2-week treatment period. After signing the consent form, participants will be randomly assigned to either the treatment (miconazole mucoadhesive tablet) group or the control (itroconazole capsule) group and the treatment period will start. During this clinic visits, participants will be given 1 weeks’ worth of miconazole mucoadhesive tablet or itroconazole capsules and daily diaries for the fortnight.

In visit 2 of 1week after, the participants will be re-evaluated on the symptom scoring, grade of clinical sign, vital signs, smear test and fungi culture). The participants will repeat 1-week treatment and record the daily diary during the following week. In visit 3 (the following day after the 2-week treatment period) and visit 4 (2-week follow up after treatment ceasing), the participant will be evaluated by performing clinical and laboratory examination as baseline.

Throughout the treatment period, other medication or therapies, such as anti-hypertension drugs, is allowed to be used on an ‘as needed’ basis. During this treatment period, participants will also be required to record their medication intake, including trial interventions, other medications intake and occurrence of adverse events to assist with compliance monitoring and acceptability of intervention. Participants will be asked to return their medication pack to enable the counting of left-overs as well as part of participant adherence monitoring.

[figure not shown]

Figure 2. Outline of trial protocol

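### The symptom-and-sign improvement rate falls to an unadjusted t or Mann-Whitney test, which makes inefficient use of the baseline scores recorded at visit 1

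*Protocol*

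**What the plan says.** Section 11.2 assigns tests by type of data. For continuous outcomes: "Continuous data were compared using either the Student t test or the Mann-Whitney nonparametric test". Binary outcomes go to chi-square or Fisher, and ordinal outcomes to a Mantel-Haenszel test. No covariate, stratum or centre term is named for any of them.

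Section 5.2 lists the clinical improvement rate as a secondary outcome. It is the fall in score divided by the starting score; the formula ends "score of symptom and clinical sign post treatment)/ score of symptom and clinical sign at baseline". The same section uses a 60% cut on this rate to separate partial response from failure.

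The baseline values exist. Section 8.3 describes visit 1 as including "baseline data collection, which include the symptom scoring, grade of clinical sign of oral candidiasis". Centre is known too: Section 4.4 recruits from "nine dental hospitals from northern, southern, western and eastern China". Section 3.3 describes blocked randomisation and does not mention stratification by centre.

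**The concern.** Dividing a change by its own baseline is a poor way to use the baseline. The divisor differs between patients, so the same movement in score counts for more in a patient who started low. The ratio also leaves in the outcome variation that a regression on baseline would remove.

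A two-sample t test on that ratio then takes no further account of where patients started. What is at stake is the width of the interval, and the power, for a secondary efficacy outcome. The information needed to do better is already on the case report form.

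**Working it through.** **1. The plan's own figure.** Section 3.2 states "an 85% efficacy rate was assumed" and "To achieve 80% power with a significance level of 10%(α level, 5%; βlevel, 20%; both 1-sided), 158 participants per group would be required". Assume equal true rates of 85% and a non-inferiority margin of 10 percentage points. The protocol states no margin, so 10 is back-solved. With one-sided alpha 0.05 and power 0.80:

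n = (1.645 + 0.842)² × 2 × 0.85 × 0.15 / 0.10² = 6.185 × 0.255 / 0.01 = 157.7, rounded up to 158 per group.

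Margins of 8, 12 and 15 points give 247, 110 and 71, so of the margins tried only 10 fits. The total of 380 follows from 316 × 1.2 = 379.2. This calculation concerns cure, not the scores; 158 per group is carried forward as the size of the comparison.

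**2. What the ratio does.** With baseline B and final score P, the rate is (B − P)/B = 1 − P/B. One point of P therefore moves the rate by 1/B. From B = 1, one point of worsening is −100%; from B = 8 it is −12.5%, an eightfold difference in weight. The values 1 and 8 are illustrative, since the protocol gives no scale range. This affects a test on means. A rank test records an extreme value only as the lowest rank.

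**3. Reference variance factors** (equal variances, correlation ρ assumed). Adjusted against unadjusted final score: 1 − ρ². Adjusted against absolute change: (1 − ρ²)/(2(1 − ρ)) = (1 + ρ)/2.

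| ρ | vs final score | vs absolute change |
|---|---|---|
| 0.2 | 0.96 | 0.60 |
| 0.3 | 0.91 | 0.65 |
| 0.5 | 0.75 | 0.75 |
| 0.7 | 0.51 | 0.85 |

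Neither comparator is the protocol's percent change, so these factors do not give the size of this point. That needs simulation.

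**4. Percent change against ANCOVA, no floor.** Assumed: 158 per group, baseline mean 6 with coefficient of variation 0.3 or 0.4 (rounded and held to 1–12), effect 0.3 SD, two-sided 5%.

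| ρ | t test on percent change | ANCOVA on final score |
|---|---|---|
| 0.2 | 57–65% | 76–78% |
| 0.3 | 62–71% | about 80% |
| 0.5 | 68–78% | 87–88% |
| 0.7 | 67–78% | about 97% |

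Setting by setting, the gain is about 9 points (87.1 − 77.7 at ρ = 0.5) to 30 points (96.6 − 67.1 at ρ = 0.7). Final scores were not stopped at zero here, so this is the favourable case. These are powers for a difference test and serve only as a measure of precision.

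**5. With a floor at zero.** Scores rounded to 0–12, same sample size and effect, ρ from 0.3 to 0.7:

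| Final scores at zero | t, percent change | Mann-Whitney, percent change | ANCOVA |
|---|---|---|---|
| 11% | 49–89% | 68–93% | 77–95% |
| 33% | 58–86% | 72–85% | 73–91% |
| 63% | 52–72% | 59–67% | 60–78% |
| 83% | 39–51% | 44–47% | 42–52% |

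A second set, with 50–85% of controls at zero, an effect of 0.35 SD and ρ from 0.2 to 0.7, put ANCOVA 2 to 15 points above the t test. Against Mann-Whitney it ranged from −2 to +9 points, and was within 4 points in 10 of 12 settings.

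**6. Cure stratified by centre.** If the centre cure rates have SD s, the variance factor is 1 − s²/(0.85 × 0.15). For s of 3, 5, 8 and 10 points this is 0.993, 0.980, 0.950 and 0.922. Power at 158 per group goes from 80.1% to 80.3%, 80.8%, 81.8% and 82.8%. The centre SDs are assumed.

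**The case against.** The strongest reply is that Section 11.2 only lists families of tests and never rules out covariates, so adjustment could be left to an analysis plan that is not shown. Part of this stands: the section does not name the improvement rate, and its Mantel-Haenszel test for ordinal data could be meant for the ratings and grades, and could be stratified. But the tests it does name for continuous data take no covariate, the improvement rate is continuous, and no stratum is given. The text therefore fixes a method that can be improved on.

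The second reply is that the gain may be small. This also stands in part. Section 3.2 assumes 85% efficacy, so many final scores may be zero. Mann-Whitney, which the plan equally permits, is not dominated by extreme percentages and gives up little in that case. ANCOVA on a score that is mostly zeros is not an obvious improvement.

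A reader might infer three stronger things that the documents do not support:

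- **That the unadjusted comparison is biased or invalid.** Under randomisation its standard error already allows for chance baseline imbalance.
- **That low-baseline patients dominate whichever test is used.** This holds for the t test only.
- **That ignoring centre seriously weakens the cure analysis.** Randomisation is not stated to be stratified by centre, so no design feature is contradicted, and the computed gain is small.

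**Conclusion.** The point holds as one of efficiency in a secondary outcome. Under Section 11.2 the improvement rate goes to an unadjusted two-sample test. If that is the t test, the loss against a baseline-adjusted analysis of the final score is roughly 2 to 30 power points across the settings tried. If it is Mann-Whitney with half or more of final scores at zero, the difference is about −2 to +9 points. With about 85% at zero there is little to choose between the methods.

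All these figures rest on assumed correlations (0.2 to 0.7), an assumed score range and spread, and assumed effects of 0.3 to 0.35 SD; the protocol gives none of them. The direction against the t test is consistent, but its size is uncertain. The change is worth making because the baseline scores are already recorded. Centre stratification for cure is a minor option.

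**What to change.** In Section 11.2, state that the post-treatment symptom-and-sign score will be compared between groups with baseline score as a covariate. Use ANCOVA, or a rank-based or ordinal model with baseline as covariate if many final scores are expected to be zero. Fix the choice, or the rule for making it, before outcome data are compared by group. In Section 5.2, keep the percent improvement rate to form the 60% response class.

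Optionally, stratify the cure comparison by centre, pooling small centres. If it is reported as a stratified risk difference with a confidence interval for the non-inferiority claim, a margin must first be stated, which the protocol does not do.

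Cost: wording in two sections and no new data. The analysed form of a secondary score outcome changes, and ANCOVA may lose about 2 power points against Mann-Whitney when most final scores are zero.

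### Section 11.2 declares non-inferiority but names only tests of no difference for binary outcomes, and no margin or decision rule is stated

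*Protocol*

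**What the plan says.** Section 11.2 of the protocol sets the framework in one sentence, "A non-inferiority statistical approach was used", and then lists tests by type of data. For continuous data: "Continuous data were compared using either the Student t test or the Mann-Whitney nonparametric test". For binary data: "For binary data, the 2 treatment groups were compared using the chi-square test or the Fisher exact test". A Mantel-Haenszel test is named for ordinal data. No margin, shifted null hypothesis, confidence-interval rule or success criterion follows.

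Section 5.1 makes clinical cure the primary outcome. Cure is a yes/no result, so the binary-data sentence governs the main comparison.

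Section 3.2 states that "an 85% efficacy rate was assumed", on the basis of itraconazole studies, and gives no rate for miconazole. It continues "To achieve 80% power with a significance level of 10" (per cent) and adds in brackets "α level, 5%; βlevel, 20%; both 1-sided". The result is that "158 participants per group would be required", raised to 380 in total for dropout. The section does not call any figure a margin.

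**The concern.** A non-inferiority claim needs a pre-stated margin and a test, or an interval, that excludes a deficit as large as that margin. Chi-square and Fisher tests, as named, have equality as their null hypothesis. Rejecting it shows a difference. Failing to reject it shows only that the data did not reveal one, which becomes more likely as the sample shrinks or the data become noisier. The stated analysis therefore does not answer the stated question.

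Two things are at stake. The planned 5% risk of wrongly accepting a worse treatment is not protected by anything in section 11.2. And a margin that is not written down could be settled after results are known, which matters in a trial where section 3.4 leaves participants, investigators and outcome assessors unblinded.

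**Working it through.** **Inputs.** From section 3.2: control rate 85%, one-sided alpha 5%, power 80%, 158 per group, 380 in total. Assumed, because the protocol is silent: miconazole rate also 85%, and equal allocation (implied by the per-group figure).

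**Step 1: reproduce 158.** For non-inferiority of two proportions with equal true rates p and margin M:

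n per group = (z_alpha + z_power)² × 2p(1 − p) / M²

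With M = 0.10: (1.645 + 0.842)² × 2 × 0.85 × 0.15 / 0.10² = 157.7, so 158. This matches the protocol.

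**Step 2: try other readings.**

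| Reading | n per group |
| --- | --- |
| Margin 8 points, one-sided 5% | 247 |
| Margin 12 points, one-sided 5% | 110 |
| Margin 15 points, one-sided 5% | 71 |
| Margin 10 points, one-sided 2.5% | 201 |
| Margin 10 points, one-sided 10% | 115 |
| Difference test, 85% vs 75%, one-sided 5% | 197 |
| Difference test, 85% vs 95%, one-sided 5% | 111 |
| Difference test, 85% vs 95%, two-sided 5%, continuity-corrected | 160 |

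The last row comes close, but it contradicts both the one-sided alpha and the non-inferiority approach. Taking the 10% as a one-sided alpha gives 115, so it did not act as the significance level in the calculation that yields 158. It fits as the margin.

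**Step 3: dependence on the unstated miconazole rate.** With n = 158, one-sided 5% and 80% power, the implied margin is

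M = (0.85 − p_mic) + 2.487 × √[(0.85 × 0.15 + p_mic(1 − p_mic)) / 158]

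- p_mic = 0.83: 0.02 + 0.103, about 12 points
- p_mic = 0.85: about 10 points
- p_mic = 0.87: −0.02 + 0.097, about 8 points

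**Step 4: what the named test would do at the margin.** True rates are 75% and 85%, with 158 per arm. The two-sided 5% chi-square is non-significant when the observed difference is smaller than about 1.96 × √(2 × 0.80 × 0.20 / 158) = 0.088. The observed difference has mean −0.10 and standard error √[(0.75 × 0.25 + 0.85 × 0.15) / 158] = 0.0447. The chance of non-significance is then about 1 − Φ((0.100 − 0.088) / 0.0447), or roughly 40%. Exact binomial enumeration, set beside a one-sided 5% Wald interval rule with a 10-point margin, gives:

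| n per arm | Chi-square non-significant | Interval rule met |
| --- | --- | --- |
| 158 | 39.5% | 5.2% |
| 190 (380 / 2, no dropout) | 31.1% | 5.1% |
| 80 (illustration) | 64.5% | 5.3% |

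**Step 5: equal treatments.** With 85% in both arms and 158 per arm, the interval rule succeeds in 80.3% of trials, which matches the planned 80% power. The chi-square is non-significant in 95.1%. In 17.2% of trials the result is non-significant but does not meet the margin, so the two approaches can lead to different conclusions.

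**The case against.** The strongest reply is that section 11.2 is a generic list of tests for all variables, and that a statistical analysis plan not shown here may supply the interval method. Part of this stands. The interval method can be left to that plan, and a reader who infers that the trial will treat p > 0.05 as proof of non-inferiority goes beyond the text, because the protocol states no such rule. But the protocol does more than leave a detail open. It declares one approach and names tests that do not serve it, and it never states the margin on which its own sample size appears to rest.

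A second temptation is to say that 158 per group proves a 10-point margin. It does not. That follows only if miconazole is also taken at 85%; Step 3 shows that two points either way moves the implied margin to about 12 or 8. Ten points is the most plausible reading, supported by the stray 10% in section 3.2.

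Nor does the missing label show that the sample size was planned without a margin. The figure reproduces as a margin-based calculation, which points to a labelling error.

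Finally, the objective in section 2 speaks only of comparison, and non-inferiority is declared only in section 11.2. That is fair, but the declaration is unqualified and the sample size fits it.

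**Conclusion.** The point holds and should be corrected before analysis. A non-inferiority approach is declared, the only tests named for binary outcomes are tests of no difference, and no margin or decision rule appears in the protocol. Those facts need no assumption.

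The size is conditional on two things that the protocol does not state: a 10-point margin (from equal 85% rates) and a reading of non-significance as success. Under both, a treatment exactly 10 points worse would be accepted in about 40% of trials at 158 per arm, or 31% at 190. That is roughly six to eight times the planned 5%. These rates measure the risk that the gap leaves open. They are not a property of a rule the protocol has adopted.

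**What to change.** **Section 3.2.** Correct the 10% significance level, which conflicts with the 5% alpha in the same sentence. State the non-inferiority margin as an absolute difference; the sponsor should confirm and justify clinically the 10 points that its sample size implies. State the assumed miconazole rate.

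**Section 11.2.** For the primary clinical cure comparison, replace chi-square and Fisher with this rule: non-inferiority is concluded only if the lower limit of the two-sided 90% confidence interval (one-sided 5%, as planned) for miconazole minus itraconazole lies above minus the margin. Report it in both the full analysis set and the per protocol set, which section 11.1 already specifies for efficacy. The interval method may be left to the statistical analysis plan. Keep chi-square and Fisher for baseline, safety and any superiority comparison.

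**Endpoint.** Name the single cure definition and time point to which the rule applies. The opening of section 5 lists candida elimination among the primary outcomes, section 5.1 has clinical cure in the short and long term, and section 5.2 defines cure as clinical response plus eradication at Day 7 or Day 14. These must be reconciled before the rule can be applied.

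**Cost.** A few sentences of protocol text, a justification for the margin and a decision on the endpoint. The sponsor is then bound to a margin stated in advance. No new patients or data are needed, and if the 10 points are confirmed with equal 85% rates, the planned alpha and power are kept.

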**12. Ethics**

12.1 Ethics review

This clinical study must follow Helsinki Declaration and related clinical research laws and regulations in China. Before research, Ethics Committee of research responsible hospital should review research scheme, and implement research scheme after signing approval documents. Suggestions of Ethics Committee should be: agree, which refers to consent after taking necessary correction; disagree, which refers to terminate or suspend approved research.

12.2 Informed consent for subjects

Before being enrolled in the research, each patient or the designated representatives should be introduced about objectives, characteristics, procedures and possible benefits and risks of the research by doctor completely and comprehensively. The patient has right to withdraw research at any time. Each patient is given a written informed consent (as an appendix in scheme) before research, and agrees its content after understanding. After signing Informed Consent, the patient can be enrolled in clinical study. As original clinical research data, the Informed Consent should be preserved for reference.

12.3 Ethics and trial registration

Written informed consent is required prior to participation from each participant or their guardian, and they will be informed of the nature of this trial including its purpose, procedures involved, expected duration, potential risks and discomfort, as well as the possible benefits they will receive from it. There is no time limit for them to ask related questions and respond to the invitation to participate. Participants will be also informed that they are free to withdraw from the study at any stage for any reason and their personal information will be undisclosed and kept securely.

The trial has also been registered with the Chinese Clinical Trial Registry (ChiCTR-TRC-13003935).

